### Procedure

Healthcare professionals at the Center of Excellence for Brain Injury and Neuropsychiatry who identify patients with an indication for treatment of social cognition problems will inform the researcher. Recruitment started on 1 January 2025. Participant recruitment is ongoing and will continue until the end of December 2026. Completion of data collection is anticipated in April 2027, and the study results are expected to be available by December 2027.

Psychologists will screen patients for eligibility based on the in- and exclusion criteria. Eligible patients will receive detailed information about the study. Then, patients will be invited to participate voluntarily during outpatient or clinical appointments. Those who consent to participate will be asked to sign an informed consent form. Upon providing informed consent, participants will be randomized to a baseline phase of varying duration, after which the T-ScEmo intervention starts, followed by maintenance and follow up phases.

Baseline measurements include a neuropsychological assessment, unless one has been conducted within six months prior to the start of the study. Furthermore, during this initial session, the therapist, together with the patient and the significant other, will formulate three treatment goals (TGA; Treatment Goal Attainment). Before, during, and after treatment participants complete multiple neuropsychological tests during a face-to-face appointment with a (trained) psychological assistant, intern or neuropsychologist. Participants and the significant other will complete a series of questionnaires digitally (see Table 1). They are free to choose when to complete the questionnaires and may pause and resume as needed.

In phases B and C, self-report scales are administered twice a week and must be completed before the next treatment session to ensure timely data collection. Post-treatment measurements will be conducted to evaluate the maintenance of treatment effects and to maintain consistency in the number of measurements across participants. A follow-up measurement will be conducted 3–5 months after treatment completion to evaluate long-term efficacy. Patients who choose not to participate will still receive T-ScEmo treatment, as it is considered standard care.

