### Hypotheses

#### Primary research question (RQ1).

Based on previous research in patients with TBI [5,21], we hypothesize that T-ScEmo will reduce social cognition problems in patients with ABI and comorbid neuropsychiatric problems. While T-ScEmo is a compensatory strategy training and thus not expected to directly improve underlying cognitive mechanisms, improvements in social behavior are anticipated due to skill acquisition, practice in daily life, and involvement of significant others. However, as the first modules specifically targets facial emotion recognition, we also expect improvements on the FEEST (i.e., emotion recognition).

We also expect improvements in social communication and interaction, as the treatment targets emotion recognition, ToM, perspective taking, awareness, inhibition of undesired social behavior and socially desired behavior. Improved compensation for deficits is expected to enhance participation in social contexts.

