** *Social cognition* **							
Social Functioning Scale (SFS)	Functioning in social situations	●	● (daily)	● (twice a week)		● (twice a week)	●
Brock’s Adaptive Functioning Questionnaire – social scales (BAFQ-SOC) [41,42]	Social monitoring, empathy	▲			▲		▲
Dysexecutive Questionnaire – social scales (DEX) [43]	Metacognition, social convention, behavioral emotional self-regulation	▲			▲		▲
Interpersonal Reactivity Index (IRI) [44]	Cognitive and affective components of empathy	▲			▲		▲
La Trobe Communication Questionnaire (LCQ) [45]	Communication quality	▲			▲		▲
Cartoon test [46]	Mental state attribution	▲			▲		▲
Facial expression of emotion: stimuli and tests (FEEST) [47]	Facial affect recognition	▲			▲		▲

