#### In- and exclusion criteria.

The in- and exclusion criteria are largely consistent with those outlined in the T-ScEmo4ALL treatment protocol [54]. A key deviation, however, is that patients with comorbid neuropsychiatric problems are not excluded from participation. Accordingly, individuals with ABI and co-occurring neuropsychiatric problems are eligible for inclusion in this study. Inclusion criteria are presented in Table 2. This table is adapted from Heegers et al. [54].

**Table 2 pone.0358008.t002:** Overview of inclusion and exclusion criteria T-ScEmo4ALL Plus^+^.

Inclusion criteria patient	Inclusion criteria significant other	Exclusion criteria
Presence of social cognitive impairments, (i.e., impairments in emotion recognition, ToM, or social behaviour>1 of 4 tests indicative and/or>1 of the (sub)scales of relevant questionnaires indicative and/or, if available, the presence of frontal lesions on CT or MRI), judged by a neuropsychologist	Preferably a life partner. If a life partner is not available, a family member or close friend	Serious neurodegenerative conditions interfering with treatment
Presence of a neurological disorder (i.e., stroke, brain tumor, TBI, infections, post-anoxic encephalopathy)	Chosen by patient	Incapacity to make informed choices, to be judged by the neuropsychologist
Presence of current neuropsychiatric problems (i.e., aggression, impulse control problems, disinhibited behavior, compulsion, and apathy)	Age > 18	Serious cognitive disorders (aphasia, amnesia, disorders in visuoperception) interfering with treatment, to be judged by a neuropsychologist
Chronic state (6 months post-injury) to minimize the influence of spontaneous recovery		No significant other available who can fill out the questionnaires
Age between 18 and 70 years of age		Not able to speak and understand the Dutch language

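### A FEEST or Cartoon score up to six months old may serve as the T0 score, so recovery before the study can be counted as reliable improvement

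*Protocol article*

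**What the plan says.** In the protocol article, Procedure: "Baseline measurements include a neuropsychological assessment, unless one has been conducted within six months prior to the start of the study". The sentence does not say which tests it covers.

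Table 1 schedules the FEEST and the Cartoon test at T0, T1 and T2. The Trail Making Test, the 15 Words Test and the Zoo Map test are scheduled at T0 only. Under Statistical analyses, the RCI is applied to the FEEST and Cartoon test among others, and is to show whether change at post-treatment and follow-up is statistically and clinically significant. The FEEST carries its own expectation under RQ1: "we also expect improvements on the FEEST (i.e., emotion recognition".

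Table 2 requires "Chronic state (6 months post-injury) to minimize the influence of spontaneous recovery". This governs the patient's inclusion, not the date of the T0 tests. The social cognition criterion in Table 2 can be met through "impairments in emotion recognition, ToM, or social behaviour>1 of 4 tests indicative", through questionnaire subscales, or, "if available, the presence of frontal lesions on CT or MRI), judged by a neuropsychologist". The four tests are not named. Screening comes before consent: "Psychologists will screen patients for eligibility based on the in- and exclusion criteria".

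**The concern.** The chronic-state criterion is there to keep spontaneous recovery out of the results. The multiple baseline protects the daily series against the same threat. The FEEST and Cartoon test have no repeated baseline, and every participant is treated, so for them the criterion is the main protection. The waiver lets their pre-score come from before the point at which that protection begins.

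If it does, recovery that took place before the patient entered the study falls inside the T0 to T1 and T0 to T2 change, and the RCI can label it reliable improvement. The error favours the treatment, and on the FEEST it bears on a stated hypothesis. Retest intervals would also differ between patients by up to half a year.

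**Working it through.** The article gives no RCI threshold or reliability, so there is no figure of its own to reproduce. The timing follows from the article. The error rates rest on assumptions, labelled below.

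**1. How old the T0 score can be.**
- Inclusion at 6 months post-injury with a score 6 months old: 6 − 6 = 0 months post-injury, as the limiting case.
- A reused score can predate the 6-month point whenever inclusion minus 6 is below 6, that is, for inclusion before 12 months post-injury.

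**2. T0 to T1 interval.** Inputs: 16 to 33 days to treatment start (Randomization), 20 to 25 weeks of treatment (Primary outcome measure), six months taken as 26 weeks, and a fresh T0 taken at the start of baseline.
- Fresh T0: 16/7 + 20 = 22.3 weeks; 33/7 + 25 = 29.7 weeks.
- Oldest permitted T0: 26 + 22.3 = 48.3 weeks; 26 + 29.7 = 55.7 weeks.

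**3. Effect of recovery on the RCI.** Assumptions: the usual RCI = (T1 − T0) / (SD·√(2(1 − r))), improvement declared above 1.96, no treatment effect, normal scores, and a mean recovery of g SD between the old test and T1. Then P(false improvement) = P(Z > 1.96 − g/√(2(1 − r))).

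| r | √(2(1 − r)) | g | threshold for Z | P |
|---|---|---|---|---|
| 0.7 | 0.775 | 0 | 1.960 | 2.5% |
| 0.7 | 0.775 | 0.2 | 1.702 | 4.4% |
| 0.7 | 0.775 | 0.5 | 1.315 | 9.4% |
| 0.8 | 0.632 | 0 | 1.960 | 2.5% |
| 0.8 | 0.632 | 0.2 | 1.644 | 5.0% |
| 0.8 | 0.632 | 0.5 | 1.169 | 12.1% |

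Over r from 0.6 to 0.9 the range is 4.1 to 6.5% for g = 0.2 and 8.1 to 20.0% for g = 0.5.

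**4. Regression to the mean, if the reused score was also the qualifying score.** The answer depends on the mean to which patients regress. The Introduction reports that 72.5 to 81.8% of patients with ABI and neuropsychiatric problems score low or very low on emotion recognition. Take this population as the reference (normal scores assumed) and select its lowest 72.5 to 81.8%, with no treatment effect and no recovery:
- r = 0.7: mean upward drift 0.10 to 0.14 SD, false improvement 3.0 to 3.3%.
- r = 0.8: mean upward drift 0.07 to 0.09 SD, false improvement 2.9 to 3.2%.

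Against 2.5% nominal, this is a small excess.

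**The case against.** **The waiver may not reach these tests.** It speaks only of a neuropsychological assessment, and the Introduction notes that routine assessments often leave out social cognition. An existing assessment may lack the FEEST and Cartoon test, and Table 3 lists face-to-face tests at T0. That is fair, but nothing in the text exempts the two tests or says that missing ones are added. The scope has to be stated.

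**The extreme is rare.** A score from soon after injury needs inclusion at the minimum and very early testing, and the article gives no distribution of time since injury. This stands against reading 48 to 56 weeks as typical. It does not remove the wider window: anyone included before 12 months is exposed to some degree.

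**The reach is limited.** Only two secondary tests are affected. The SFS, NPS and RQS have their own daily baselines, and the visual analysis and randomization tests for those series do not use the T0 tests. This is correct and bounds the point.

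**A stronger reading that does not hold.** A reader might infer that reused scores were selected for being low, so that regression to the mean inflates the RCI substantially. For a score at the 5th percentile and r = 0.7 to 0.8, one can compute 6.5 to 7.6% false improvers. That figure requires patients to regress to the mean of the norm group. Low emotion-recognition scores are typical of this population, so selecting on them selects little, and the figure should not be used. Nor does the article say that eligibility scores are reused: the four tests are unnamed, and questionnaires or imaging can also qualify a patient. For the Cartoon test it gives no comparable percentage, so the size there is unknown.

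**Conclusion.** The timing defect holds. The two six-month rules together let a FEEST or Cartoon pre-score predate the chronic state in patients included 6 to 12 months post-injury, and stretch the T0 to T1 interval to at most 48 to 56 weeks instead of 22 to 30. This needs no assumption beyond counting six months as 26 weeks and the waiver covering these tests, which its wording allows.

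The size is conditional. With 0.2 to 0.5 SD of recovery and r of 0.7 to 0.8, false reliable improvement is about 4 to 12% per affected patient and test, against 2.5%. How many patients are affected cannot be known from the article. Regression to the mean is a possible, smaller addition only where the reused score also qualified the patient. The point is worth correcting because the bias runs towards benefit on a stated hypothesis, but it does not touch the primary outcome.

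**What to change.** State which tests the waiver covers, and from which date the six months are counted, since the start of the study could mean the patient's own start or the study's.

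Limit the waiver to the tests given at T0 only: the Trail Making Test, the 15 Words Test and the Zoo Map test. Alternatively, accept a reused FEEST or Cartoon score only if it was obtained at least 6 months post-injury and close to the start of baseline. Otherwise give both tests at T0, as Table 1 already schedules.

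For patients already enrolled with a reused score, report its date and the time since injury at that date, and give the RCI results with and without these scores.

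The cost is one session with two tests for patients who would have been waived, with one more exposure and so some practice effect, which also pushes towards improvement. The sensitivity analysis has fewer RCI results, which matters with a minimum of 8 patients. Recruitment runs to the end of December 2026, so fresh testing may reach only the last patients; the reporting and the sensitivity analysis need no new data.

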### Primary outcome measure

*Satisfaction with social functioning* is assessed using a Social Functioning Scale (SFS), in which patients and significant others rate the patient’s functioning in social situations on a 10-point Likert scale ranging from 1 (“not at all”) to 10 (“entirely”). The item presented is: “How satisfied are you today with your (or your significant other’s) functioning in social situations?” To ensure a sufficient number of data points, as recommended for SCED studies, the SFS will be completed frequently: daily during phase A (2–4 weeks) and twice per week during phases B (20–25 weeks) and C (13–21 weeks). The SFS will be completed by both the patient and a significant other online (M-Path).

### Sample size

We aim to include at least 8 patients and their significant others (i.e., 16 participants in total), with a maximum of 20 patients and their significant others (i.e., up to 40 participants). According to Tate et al. (2019) [56], a minimum of 3 participants is generally recommended to ensure sufficient variability and reliability of the data, as well as meet evidence standards. Moreover, replication across at least 3 participants is essential to draw robust conclusions. Given that the study design consists of 3 different baseline lengths – each considered a separate experiment in terms of the SCED design standards – it is ideal to include at least 3 participants per 3 baseline condition (i.e., a total of 9 participants) [56].

### Data analysis

Descriptive analyses (count, percentage, median, and range) will be performed to describe sociodemographic (e.g., age, sex), clinical (i.e., types of ABI, time since ABI, DSM-5 classifications), and treatment characteristics (i.e., therapists involved, adjustments to standard treatment protocol, total number of sessions, dropout).

A wide variety of analytic techniques is available for evaluating data from SCED studies, including both visuals analysis and statistical methods.

#### Visual analyses.

As a first step, we will present the SCED data graphically and use visual inspection to determine whether differences between phases are apparent. The underlying assumption is that if differences are not visually apparent, they are unlikely to be statistically significant and clinically meaningful. Scores on frequently administered measures will be plotted graphically for each participant using the Shiny app for Single-Case Data Analysis (Shiny SCDA) in R [57,58] and analyzed visually. Intervention-related changes in outcome measures and the duration of change will be assessed based on the procedure described by Lane and Gast (2014) [59]. Visual analyses will focus on level, trend, variability, and overlap (i.e., extent of data overlap across phases). Evidence for a functional relationship will be categorized as follows: strong evidence (at least three demonstrations of the intervention effect and no demonstration of no effect), moderate evidence (at least three demonstrations of the intervention effect with at least one demonstration of no effect), and no evidence (fewer than three demonstrations of the intervention effect).

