#### Randomization.

The multiple baseline design will be used to strengthen internal validity by controlling for threats such as history and maturation (i.e., in the case of brain injury spontaneous or natural recovery should be considered). Three different baseline lengths will be used: start treatment within 16–20 days, 21–27 days, or 28–33 days. This setup ensures that no participant waits longer than 4 weeks before starting T-ScEmo treatment, which aligns with the average waiting period for non-participating patients. The participants are randomly assigned to a baseline length by using a randomization tool. Randomization applies only to baseline length; all participants receive the intervention.

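### The visual-evidence rule ignores baseline length, so three demonstrations from a single length can be graded moderate evidence of a functional relationship

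*Protocol article*

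**What the plan says.** All references are to the protocol article.

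- **Visual analyses.** The rule has three grades. Strong needs three or more demonstrations and none of no effect. The middle grade is "moderate evidence (at least three demonstrations of the intervention effect with at least one demonstration of no effect"). The lowest is "no evidence (fewer than three demonstrations of the intervention effect"). None of them mentions baseline length or start time.
- **Randomization.** The purpose of the stagger is explicit: "The multiple baseline design will be used to strengthen internal validity by controlling for threats such as history and maturation". The lengths are also given: "Three different baseline lengths will be used: start treatment within 16–20 days, 21–27 days, or 28–33 days". On allocation the text says only "The participants are randomly assigned to a baseline length by using a randomization tool", without probabilities or balancing.
- **Sample size.** "We aim to include at least 8 patients and their significant others (i.e., 16 participants in total), with a maximum of 20 patients". Each length is "each considered a separate experiment in terms of the SCED design standards", and "it is ideal to include at least 3 participants per 3 baseline condition (i.e., a total of 9 participants").
- **Statistical analyses.** NAP is calculated only after strong or moderate evidence. Randomization tests and regression are also planned and do not depend on the visual grade. Statistical analysis as a whole is described as complementary.

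**The concern.** A multiple-baseline design separates a treatment effect from a time effect in one way: change follows the start of treatment at different baseline lengths. A grade of functional relationship should use that information, and this rule does not.

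Suppose ratings shift in everyone about 16–20 days after their own entry, for example because people adapt to rating themselves daily. Patients who start treatment in the first window appear to respond. Patients in the two longer baselines shift while still untreated, so they do not demonstrate an effect. Taken together this is evidence against treatment as the cause. Under the written rule the longer-baseline patients only lower the grade from strong to moderate, however many there are, provided three patients in the first window demonstrate.

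The Sample size section does not repair this. It also counts participants, and by treating each length as its own experiment with three patients as the ideal, it lets one length supply all three demonstrations.

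At stake are the evidence category that will be reported and the decision to calculate NAP.

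**Working it through.** **The plan's own figures.** 3 lengths × 3 patients = 9; 8 × 2 = 16 participants; 20 × 2 = 40. All agree with the text. The article gives no error rate for the evidence rule, so there is none to reproduce.

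**Inputs.** From the article: three start windows; 8 to 20 patients; a threshold of three demonstrations. Assumed: independent allocation with probability 1/3 to each length; one patient is one possible demonstration; no treatment effect; a shift early in the study that coincides with the first window.

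**Current rule.** Let s be the proportion of first-window patients in whom the shift is visible. With no demonstrations elsewhere, the number of demonstrations is Binomial(N, s/3), and the rule fires when it is at least 3.

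At N = 8 and s = 1: 1 − (256 + 1024 + 1792)/6561 = 1 − 3072/6561 = 0.532. The case where all eight patients fall in the window (graded strong) is (1/3)^8 ≈ 0.0002, so nearly all of this is moderate.

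| N | s = 1 | s = 0.9 | s = 0.8 |
|---|---|---|---|
| 8 | 0.53 | 0.45 | 0.36 |
| 9 | 0.62 | 0.54 | 0.45 |
| 12 | 0.82 | 0.75 | 0.66 |
| 20 | 0.98 | 0.96 | 0.93 |

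Other sensitivities at N = 8, s = 1:
- If allocation is weighted by days in the window (5 of 18 for the first), the figure is 0.39.
- With only 7 analysable patients it is 0.43.
- The figure drops below one half once s is under about 0.96.

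**Balanced allocation without a rule change.** At 3/3/2 the first window holds three patients with probability 2/3, so the figure rises to 0.67. At 3/3/3 it is 1.00. Both use s = 1.

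**Two-length rule.** Let q be the chance that a patient in another window demonstrates by chance. Put a = 1/3, b = q/3 and z = 1 − a − 2b, with s = 1.
- Current rule: P(Binomial(N, a + 2b) ≥ 3).
- Two-length rule: that figure minus Σ over k ≥ 3 of C(N,k)(a^k + 2b^k) z^(N−k), which removes the cases where all demonstrations come from one length.

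| q | N = 8, current | N = 8, two lengths | N = 20, current | N = 20, two lengths |
|---|---|---|---|---|
| 0 | 0.53 | 0 | 0.98 | 0 |
| 0.05 | 0.61 | 0.18 | 0.99 | 0.49 |
| 0.10 | 0.68 | 0.35 | 1.00 | 0.75 |

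**Empty length.** At N = 8 with independent allocation: 3(2/3)^8 − 3(1/3)^8 = 0.117.

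**Cost in sensitivity.** Take 3/3/2 allocation and half of patients responding. The current rule gives at least moderate with probability 219/256 = 0.855. The two-length rule loses only the two patterns in which exactly one full group of three responds, 2/256, leaving 217/256 = 0.848.

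**The case against.** **The probabilities describe a constructed scenario.** This stands. They need a shift on the same study days in every patient, confined to one window. Nothing in the article shows that one occurs. The chronic-state inclusion criterion limits spontaneous recovery, and the non-concurrent design means a calendar event would not fall on the same study day across patients. Time since entry remains the relevant clock.

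**A reader might infer that the rule gives a false moderate grade more often than not.** The article does not support that. The figures are conditional on the shift, and at 8 patients even the conditional figure falls below one half with slightly imperfect visibility. The scenario also does not carry over to a late shift: at days 28–33 the patients in the two earlier windows are already in treatment and could look like delayed responders.

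**A reader might infer that the grade determines the trial's main conclusion.** No section says so. Visual analysis is presented as a first step, every patient is plotted, and the randomization tests run whatever the grade. That is a real safeguard for the overall conclusion. It does not change the category, and the category alone opens the NAP step.

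**The cited visual-analysis procedure may restrict what counts as a demonstration.** That cannot be seen here. The rule as printed contains no such restriction.

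**Conclusion.** The point holds as a structural defect in a stated rule. The grade of functional relationship does not use the stagger that the Randomization section relies on, so a pattern confined to one baseline length can be graded moderate. This follows from the text and needs no probability assumption.

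The size is illustrative. Given an early time-since-entry shift that coincides with the first window, and independent 1/3 allocation, the probability of a moderate grade is 0.53 at 8 patients and 0.98 at 20 with full visibility, and 0.36 and 0.93 with 80% visibility. How likely such a shift is cannot be judged from the article. The rule should be amended, and this can still be done without knowledge of results: data collection is expected to run to April 2027, and the investigator is not to analyse any data before it is complete.

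**What to change.** Amend the rule in Visual analyses as follows:

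1. Moderate requires at least three demonstrations from at least two baseline lengths.
2. Strong requires all three lengths to be represented, in addition to the existing condition. Since strong already allows no demonstration of no effect, this mainly guards against an empty length.
3. Change that begins before treatment start counts as evidence against the effect.
4. The grade is reported with a table of demonstrations by baseline length.

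Block any remaining allocations so that no length is empty, but only together with the rule change. Blocking alone makes the single-window problem worse.

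The two-length rule reduces the problem without removing it. Its benefit shrinks as chance demonstrations become more common and as the sample grows, so the table by length is needed whatever the grade.

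The cost is one amended rule, one table and a blocked list. The grade becomes slightly stricter: 0.855 to 0.848 for at least moderate under the assumptions shown.

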#### Statistical analyses.

Statistical analyses of SCED data have gained prominence in recent years and will be used as a complementary method of data evaluation. There are still, however, no agreed-upon criteria for statistical analysis of SCED data [60]. Data from the frequently administered measures will be displayed and analyzed using the Shiny app for Single-Case Data Analysis [57]. The generated graphs will support visual analysis, and regression analysis will be conducted for quantitative assessment. Randomization tests (RTcombiP; [61]) will be applied to evaluate if levels of social cognition problems, social communication, social interaction, social problems, and neuropsychiatric problems differ significantly between phases (baseline versus treatment + follow-up).

If visually analysis yields strong or moderate evidence, effect size estimates will be calculated using non-overlap of all pairs (NAP) for the dependent variables: social cognition problems, social interaction, social communication, neuropsychiatric problems, and neuropsychiatric problems. To assess individual improvements on the periodic measurements (BAFQ, DEX, IRI, FEEST, Cartoon test, LCQ, DMSCQ, NPI-Q), the Reliable Change Index (RCI) will be calculated. The RCI will indicate whether post-treatment and follow-up changes are both statistically and clinically significant.

Reporting of the study will follow the Single-Case Reporting guideline In Behavioral interventions (SCRIBE) checklist [53], consisting of 26 items that outline the structure of a SCED report.

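### Three demonstrations earn a moderate grade whether 8 or 20 patients are enrolled, and NAP is calculated only after a favourable visual grade

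*Protocol article*

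**What the plan says.** Under Visual analyses, the top grade is "strong evidence (at least three demonstrations of the intervention effect and no demonstration of no effect". The middle grade is "moderate evidence (at least three demonstrations of the intervention effect with at least one demonstration of no effect". Fewer than three demonstrations count as no evidence. None of the three definitions refers to the number of patients, and the middle one puts no ceiling on cases without an effect.

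Under Sample size, the aim is "We aim to include at least 8 patients and their significant others (i.e., 16 participants in total". The same sentence sets the upper limit on enrolment: "with a maximum of 20 patients and their significant others". The number three appears there as a floor: "replication across at least 3 participants is essential to draw robust conclusions".

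Under Statistical analyses, the effect size depends on the grade: "If visually analysis yields strong or moderate evidence, effect size estimates will be calculated using non-overlap of all pairs (NAP". Regression and randomization tests are planned in the same section without that condition, as a complement to the visual analysis.

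**The concern.** Three is introduced as the least replication needed, but the grading rule makes it sufficient at any sample size. The moderate grade then says little about how consistently the treatment works. Three of 8 is 38% of patients; three of 20 is 15%, with 17 showing no effect. The strong grade shifts the other way, because each added patient is another chance of the one non-demonstration that removes it. The conclusion therefore depends partly on enrolment.

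The gate on NAP is a second problem. An outcome graded as no evidence gets no effect size, so the NAP values that exist have been chosen by a favourable visual result. The article justifies looking first by assuming that effects not visible are unlikely to be significant or meaningful. With the gate in place, NAP cannot test that assumption. A reader pooling or comparing the published values would start from a selected set.

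**Working it through.** **The plan's own figure.** The only number given in support is the ideal sample: 3 patients × 3 baseline lengths = 9, which reproduces "it is ideal to include at least 3 participants per 3 baseline condition (i.e., a total of 9 participants". No error rate is stated for the visual rule.

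**Inputs.** N = 8 and 20 (Sample size); threshold of three (Visual analyses). Assumptions not in the article: the patient is the unit, patients are independent, every patient is classed as either a demonstration or a non-demonstration, and p is the chance that a patient with no effect is judged to show one. A range is shown for p because cases are judged qualitatively on level, trend, variability and overlap.

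**Unit.** If the units were the three baseline lengths, the moderate grade could never occur, since it needs three demonstrations plus one non-demonstration, that is at least four units. The patient is the workable reading.

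**Chance of a positive grade with no true effect**, per outcome and rater:

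P(X ≥ 3) = 1 − Σ(k = 0 to 2) C(N,k) p^k (1 − p)^(N−k)

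- N = 8, p = 0.10: 1 − (0.4305 + 0.3826 + 0.1488) = 0.038
- N = 20, p = 0.10: 1 − (0.1216 + 0.2702 + 0.2852) = 0.323, allowing for rounding of the terms

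| N | p = 5% | p = 10% | p = 20% |
|---|---|---|---|
| 8 | 0.6% | 3.8% | 20% |
| 20 | 7.6% | 32% | 79% |

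Practically all of this falls in the moderate grade, because strong needs all N patients (0.2^8 = 2.6 × 10⁻⁶).

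**Count needed to keep this chance at or below 5%**, for p = 5%, 10%, 20%: 3, 3, 5 with 8 patients and 4, 5, 8 with 20. No single count serves both sample sizes.

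**Chance of the strong grade** if each patient independently shows an effect with probability 80% (assumed): 0.8^8 = 0.168, or 17%, with 8 patients; 0.8^20 = 0.012, or 1%, with 20.

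**Selection of NAP.** Simulation of 400 cohorts per setting with no effect in any patient (true NAP 0.50). All settings are assumed: daily first-order autoregressive scores with correlation φ, baselines of 18, 24 or 30 days, 44 twice-weekly treatment points, and a demonstration counted when NAP ≥ 0.66.

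| N | φ | Cohorts passing the gate | Mean NAP in those passing |
|---|---|---|---|
| 8 | 0.3 | 0% | none passed |
| 8 | 0.7 | 9% | 0.567 |
| 8 | 0.85 | 22% | 0.570 |
| 20 | 0.3 | 3% | 0.525 |
| 20 | 0.7 | 53% | 0.518 |
| 20 | 0.85 | 83% | 0.511 |

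Without the gate, the mean over all cohorts was 0.50 in every setting. The 3% cell is only about 13 cohorts, so its mean is imprecise.

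**The case against.** Several points on the other side stand.

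- The false-demonstration rate is assumed. At the planned minimum of 8 with p = 10% the chance is 3.8%; 32% and 79% need the ceiling of 20, whereas 9 is called ideal.
- The unit is not stated, and each baseline length is described as a separate experiment. Graded within one group of about 7 (20 ÷ 3), the chance is 2.6% at p = 10% and 14.8% at p = 20%.
- With independent errors and no effect in any patient (20 baseline and 44 treatment points, same cut-off), the gate opens in 0.07% of simulated studies at N = 8 and 0.8% at N = 20. Frequent chance passes need serial correlation or a looser visual judgement.
- Randomization tests and regression do not depend on the visual grade, every participant's series is plotted, and de-identified data are to be released.
- The investigator may not analyse data before collection is complete.

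Stronger readings are tempting but not supported. A reader might infer that null or negative NAP values will never appear. The gate is on the overall grade, and NAP is then calculated for the dependent variables without restriction to responders, so patients without an effect also get a value once it opens. A reader might infer that both problems worsen with enrolment; the NAP bias in fact shrinks. A reader might also cite a simulation with real differences between patients (between-case SD 0.6), where the gate opens in 19% of studies with 8 patients and the mean NAP is 0.57. Those demonstrations come almost entirely from patients with a true positive effect, so the figure does not measure chance findings.

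The stated rules remain: a count that ignores N, and an effect size calculated only after a favourable result. The ungated tests are complementary and do not alter the grade.

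**Conclusion.** The point holds as a defect in grading and reporting. In direction it needs little assumption: for any given p between 0 and 1, a chance moderate grade becomes more likely as patients are added, and a strong grade becomes rarer unless every patient responds. The size rests on an assumed p and on the patient as unit: from 0.6% to 20% with 8 patients and from 7.6% to 79% with 20, for p from 5% to 20%. Selection of NAP is certain as a rule, because outcomes graded as no evidence get none. Its size is modest and model-dependent: about +0.07 with 8 patients under strong autocorrelation, and +0.01 to +0.025 with 20. The documents do not support saying that all quantitative results hang on the visual verdict.

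**What to change.** Under Statistical analyses, delete the condition on the visual grade. Calculate and report NAP with a confidence interval for every patient, rater and repeatedly measured outcome, whatever the grade.

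Under Visual analyses, state that the patient is the unit, if that is intended. Report each grade with the number of demonstrations over the number of cases, and do not let moderate stand without that fraction.

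A proportion-based threshold is an option if it is fixed before any data are analysed, but the documents support no particular cut-off. There is still time, since the investigator does not analyse until data collection ends, anticipated in April 2027.

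The cost is a few sentences and a little more computation on data already being collected. The results may look less favourable.
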